## Abstract

**Background:**

Patient education and self-management programs are offered in many countries to people with chronic conditions such as osteoarthritis (OA). The most well-known is the disease-specific Stanford Arthritis Self-Management Program (ASMP). While Australian and international clinical guidelines promote the concept of self-management for OA, there is currently little evidence to support the use of the ASMP. Several meta-analyses have reported that arthritis self-management programs had minimal or no effect on reducing pain and disability. However, previous studies have had methodological shortcomings including the use of outcome measures which do not accurately reflect program goals. Additionally, limited cost-effectiveness analyses have been undertaken and the cost-utility of the program has not been explored.

**Methods/design:**

This study is a randomised controlled trial to determine the efficacy (in terms of Health-Related Quality of Life and self-management skills) and cost-utility of a 6-week group-based Stanford ASMP for people with hip or knee OA.

Six hundred participants referred to an orthopaedic surgeon or rheumatologist for hip or knee OA will be recruited from outpatient clinics at 2 public hospitals and community-based private practices within 2 private hospital settings in Victoria, Australia. Participants must be 18 years or over, fluent in English and able to attend ASMP sessions. Exclusion criteria include cognitive dysfunction, previous participation in self-management programs and placement on a waiting list for joint replacement surgery or scheduled joint replacement.

Eligible, consenting participants will be randomised to an intervention group (who receive the ASMP and an arthritis self-management book) or a control group (who receive the book only). Follow-up will be at 6 weeks, 3 months and 12 months using standardised self-report measures. The primary outcome is Health-Related Quality of Life at 12 months, measured using the Assessment of Quality of Life instrument. Secondary outcome measures include the Health Education Impact Questionnaire, Western Ontario and McMaster Universities Osteoarthritis Index (pain subscale and total scores), Kessler Psychological Distress Scale and the Hip and Knee Multi-Attribute Priority Tool. Cost-utility analyses will be undertaken using administrative records and self-report data. A subgroup of 100 participants will undergo qualitative interviews to explore the broader potential impacts of the ASMP.

**Discussion:**

Using an innovative design combining both quantitative and qualitative components, this project will provide high quality data to facilitate evidence-based recommendations regarding the ASMP.

## Background

Osteoarthritis (OA) is a common chronic disease that poses particular challenges to patients and health professionals as there is currently no cure for the condition. Consequently, the majority of chronic disease care and management is undertaken by the individual who may only have brief and infrequent interactions with the health care system. Effective management of OA therefore requires *self-management *of the condition. Patient education programs aim to impart knowledge and skills to individuals so that they may better manage their arthritis. A widely-recognised program is the Arthritis Self-Management Program (ASMP), developed at the Stanford University Medical Centre in the early 1980s by Lorig and colleagues [1]. The program addresses pain management, healthy behaviours, communication with doctors and disease-specific information [2]. An important aspect of the program is the bringing together of individuals in a similar situation for mutual support and to foster a sense of self-efficacy [3,4]. Self-efficacy is based on social cognitive theory [5] and relates to an individual's confidence and ability to perform healthy behaviours.

Osborne et al [6] described the core concepts promoted in patient self-management as:

• engagement in activities which promote health, build physiological reserve, and prevent adverse sequelae;

• appropriate interaction with healthcare providers and adherence to recommended treatments;

• monitoring of physical and emotional status and making appropriate management decisions on the basis of the results of self-monitoring; and

• management of the effects of illness on an individual's emotions, self-esteem, relationships with others and ability to function in important roles.

A key criticism of previous studies evaluating the ASMP is the use of outcome measures which do not accurately reflect the goals of the programs. Table 1 presents the pooled effect sizes from recent meta-analyses of studies evaluating self-management education programs (not restricted to the Stanford ASMP). Earlier studies have focussed on measures of pain and disability [7-9], which overall, have remained unchanged or only slightly improved after self-management programs. A small beneficial effect of self-management on psychological outcomes was reported [10]; although only 3 studies used the Stanford ASMP model and variability in the individual effect sizes (range -0.19 to 0.33) means that firm conclusions cannot be drawn. Most recently, a large study conducted in the United Kingdom reported significant improvements in anxiety and self-efficacy following an arthritis self-management program, although the mean gains were small and unlikely to be clinically important [11].

As non-specific chronic disease self-management programs have been found to be beneficial for other patient groups in terms of reduced blood pressure, fewer asthma attacks and lower blood glucose levels [8,9], it is likely that the outcomes of the ASMP are yet to be appropriately and comprehensively assessed. This is supported by Newman et al [12], who considered that the ASMP was primarily directed towards strategies to cope with symptoms and their sequelae, rather than the reduction of pain and disability. Thus, the ASMP focuses on changing an individual's perceptions of pain and the development of strategies to manage the disabling effects of arthritis. The intended impact of the program would therefore be better described as improving an individual's self-management skills set, enhancing their knowledge of arthritis and appropriate use of healthcare and further down the causal chain, improving their Health-Related Quality of Life (HRQoL). These constructs have been poorly-measured to date but could provide valuable information about the potential broader impacts of the ASMP.

Another limitation of earlier studies investigating the ASMP has been the use of unrepresentative samples. Much of the initial research was undertaken by the developers of the ASMP using randomised convenience samples recruited from the community [1,13]. Such samples are unlikely to be representative of the wider population with OA, particularly with respect to the level of education attained. For example, the largest study included 695 individuals where 73% of the sample had more than 12 years of education and of these, 29% had more than 16 years of education [13]. Previous studies have used heterogeneous study samples which have included people with OA, rheumatoid arthritis and fibromyalgia [7]. Further research involving representative and well-characterised samples is required to improve the generalisability of the results.

Although current Australian and international clinical guidelines promote the concept of self-management for osteoarthritis [14,15], there is presently little evidence to support the ASMP. This lack of evidence may be a barrier to clinicians referring patients to the program. Our earlier research has shown that ASMPs are under-utilised by people with arthritis and that only a small proportion of self-management referrals come from health professionals [6,16]. While the ASMP has been applied in some community settings for many years, its overall impact on the wellbeing of people with OA remains unknown. The present study will provide much-needed data on the efficacy of the ASMP with respect to HRQoL and self-management skills sets; it will also evaluate the cost-utility and applicability of this intervention for people with lower limb OA.

## Methods/design

### Aim

The primary aim of this study is to determine the efficacy of a 6-week, group-based ASMP on HRQoL and self-management skills in people with hip or knee OA.

### Study design

This study is a randomised controlled trial with a 12 month follow-up period. Although the blinding of participants would be ideal, we did not consider this feasible as the possibility of attending a 6 week program needs to be explained to potential participants in order to ascertain their willingness to take part in the study.

In the present study, participants will be allocated to an intervention group who will undergo the Stanford ASMP and receive an arthritis self-management book [2] or to a control group who will receive the book only. The study has both quantitative and qualitative components; an overview of the recruitment method, randomisation process and follow-up procedures is provided in Figures 1 and 2.

### Ethics

Ethics approval has been received from the Human Research Ethics Committees of Barwon Health, Cabrini Hospital, Epworth Hospital and The University of Melbourne.

### Eligibility criteria

The eligibility criteria for this study are listed in Table 2. Determination of eligibility will involve a two-step process commencing with review of the potential participant's medical record and subsequent telephone screening. A diagnosis of hip or knee OA will be extracted from radiology reports; where this information is not stated explicitly, medical records and radiographs will be used to diagnose OA according to American College of Rheumatology criteria [17,18]

### Identification and recruitment of study participants

Six hundred participants referred to an orthopaedic surgeon or rheumatologist for hip or knee OA will be recruited from outpatient clinics at 2 public hospitals and community-based private practices located within 2 private hospital settings in Victoria, Australia. Potentially eligible individuals will be identified by both retrospective review of recent medical records and prospective identification of consecutive presentations attending orthopaedic surgeons and rheumatologists associated with the study hospitals. Due to differences in the structure of public and private health care systems in Australia, the recruitment procedure at each of the sites will be slightly different. At the private practices, identification of potentially eligible participants will be undertaken by the treating specialist and a letter inviting participation will be provided. Written consent will be required before contact can be made by the researchers. At the public hospital sites, potentially eligible participants will be sent an information letter and then contacted by a researcher. The recruitment and screening process is summarised in Figure 2.

A researcher will then telephone potentially eligible participants to provide detailed information about the study. At this time, a screening form will be completed to verify that the individual meets the eligibility criteria. Potential participants will be asked about their preferences for ASMPs with respect to scheduling and the preferred format of the program (eg 6-week course or provision of a book). Individuals who do not provide verbal consent will be asked to list up to three reasons for not participating in the study. This information will be used to estimate the feasibility of conducting the ASMP in a 'real world' setting and for translating the program into clinical practice.

People who meet the specified eligibility criteria and provide verbal consent will then be sent a consent form and baseline questionnaire.

### Randomisation

Once a completed consent form and baseline questionnaire have been returned to the researchers, the participant is considered to have entered the study and will be randomised to either the intervention or control groups, stratified by study site. For each site, a computer-generated random numbers table will be used to assign group allocation according to permuted blocks of 4 or 6. A second randomisation procedure, stratified by treatment group, will be used to select a subgroup of 100 participants who will undergo up to 2 qualitative telephone interviews (conducted at baseline and 6 weeks, or 6 weeks only).

Group allocation will be concealed using opaque sealed envelopes. Upon receipt of a completed consent form and baseline questionnaire, the group allocation envelope will be opened at the study co-ordinating centre (Centre for Rheumatic Diseases, The University of Melbourne) by a research assistant not associated with this study. To further ensure the integrity of the treatment allocation, this process will be observed by a second staff member and recorded with a signature and date. At this point, participants will be informed of their group allocation.

### Intervention

The active intervention group will take part in the Stanford ASMP. The program consists of a weekly 2.5 hour session for 6 weeks. The program will be held in a variety of locations in metropolitan Melbourne and Geelong and at a variety of times (day, evening, weekday and weekend) to maximise attendance. Each course will have up to 12 participants. The course is delivered in a prescriptive format by two leaders and covers the following key areas [6]:

• management of pain and fatigue

• physical activity

• medication usage

• managing anger, fear and frustration

• solving health-related problems

• communication with doctors

For this study, one peer leader (who has arthritis or personal experience of arthritis) and one health professional leader (for example, a nurse or physiotherapist) will be used. This model has worked well in our pilot research and anecdotal reports indicate that this method may be preferred by referring clinicians. Course leaders who have undergone training in the Stanford ASMP model will be recruited and additional leaders (where required) will be trained according to the Stanford course leader protocol. Regular course leader meetings will be held to ensure standardised leader quality and high retention rates.

Participants will also receive an arthritis self-management book [2]. Although the primary component of the ASMP is group-based education and close interaction with 'like' individuals, the course also encourages directed home-based learning and practice of skills learned in the sessions. These activities are supported by the arthritis self-management book.

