### Control

The control group will not receive the ASMP but will be sent an arthritis self-management book [2]. There is currently no evidence to suggest that provision of this book alone is beneficial, although to date, this has only been assessed in one study which investigated the effect of the ASMP for people with OA, rheumatoid arthritis or fibromyalgia [19]. After 4 months, no change in pain, self-efficacy, disability or mental health was observed for the control group which received the Arthritis Self-Help book only.

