### Sample size considerations

The sample size calculations for this study are based on the primary outcome measure (AQoL instrument). Our pilot research involving people with OA (*n *= 39) showed a mean (SD) improvement in the 6-month AQoL score of 0.04 (0.21) following the ASMP. Given that some of this sample had end-stage joint disease for which conservative management was unlikely to be effective, we expect the effect of the ASMP to be larger than this in people with less severe OA. It is also important to note that the proportion of participants who reported a substantial benefit (an increase in AQoL score of greater than 0.05 utility units) was about 43%, whereas substantial decline occurred in 20% of participants. Using the proportion of people who report an improvement of more than 0.05 AQoL utility units as an outcome, a sample size of 600 (300 participants in each group) will provide sufficient power to detect an additional 10% of participants in the intervention group reporting a minimal important improvement (assuming 30% of control group who report improvement, beta = 0.80, alpha = 0.05, two-tailed).

No data are available on the proportion of people who might experience a clinically important improvement in HRQoL over the study period without receiving the active intervention, although earlier RCTs conducted by the developers of the ASMP have found minimal improvement for no-treatment control groups for up to 1 year (average improvement <2% for pain and <1% for depression) [34,35]. Based on the findings of Solomon et al [19], provision of the arthritis self-management book to the control group in the present study is anticipated to have a negligible impact. However, given the labile nature of OA, it is possible that the control group may experience fluctuations in wellbeing over the study period. Therefore, a 10% advantage for the intervention group is considered to be a conservative estimate of benefit.

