### Planned statistical and qualitative analyses

An intention-to-treat analysis will be performed using all randomised participants who provide any post-baseline data [36].

The intervention and control groups will be examined for baseline comparability with respect to demographic and other factors. Analysis of covariance will be used to assess differences in 12 month outcomes between groups after adjusting for baseline differences. Repeated measures analysis using linear mixed models will assess the constancy of any effects of the ASMP over time.

A cost-utility analysis will be undertaken as part of this research. Standard economic evaluation for clinical trials will be used to assess differences in resource use and health outcomes between groups [37]. The incremental cost or savings per extra person with a clinically significant improvement per Quality-Adjusted Life Year (QALY) compared to the control group will also be calculated. A clinically significant improvement in HRQoL will be regarded as a utility change of at least 0.05 AQoL units [22].

Qualitative analysis techniques will be used for data obtained from the telephone interviews. Interview tapes will be transcribed for analysis; coding of transcripts and any supplementary written notes will be performed using codes developed from the data. Data analysis will be ongoing and will run parallel to the data collection with the objective being to transcribe data from the interview before moving onto the next interview (where feasible). Thematic analysis from the transcripts will be used and results will be discussed according to themes identified from the data.

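### Only the intervention arm is taught in groups, yet the named 12-month analysis and the sample size treat all 600 participants as independent, so standard errors and power are too optimistic if outcomes correlate within courses

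*Protocol article*

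**What the plan says.** Under Randomisation in the protocol article, individuals "will be randomised to either the intervention or control groups, stratified by study site". The Intervention section then places the intervention arm in courses: "Each course will have up to 12 participants". On delivery it says: "The course is delivered in a prescriptive format by two leaders and covers the following key areas". It also states that "the primary component of the ASMP is group-based education and close interaction with 'like' individuals", and the Background makes a similar point: "An important aspect of the program is the bringing together of individuals in a similar situation for mutual support". The Control section has no group element: "The control group will not receive the ASMP but will be sent an arthritis self-management book".

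Under Planned statistical and qualitative analyses, the between-group comparison is fixed in one sentence: "Analysis of covariance will be used to assess differences in 12 month outcomes between groups after adjusting for baseline differences". A linear mixed model is also named, but only to examine whether effects hold over time. Neither model has a term for course or leader. Under Sample size considerations, "a sample size of 600 (300 participants in each group) will provide sufficient power" for a 10-point difference in the proportion improving, from 30% in controls. No ICC, design effect or course size enters that calculation.

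**The concern.** This is a partially nested design: treatment is delivered in groups in one arm and to separate individuals in the other. Members of a course share leaders, venue, time slot and each other, and the article presents that interaction as part of the programme's primary component. A positive within-course correlation is therefore plausible, although the article does not estimate one.

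If it exists, 300 intervention participants carry less information than 300 independent people. An analysis that ignores course then reports intervals that are too narrow, and the error leans towards declaring a benefit. The same applies to the secondary outcomes and to the cost and QALY comparisons. The trial is meant to inform referral and funding decisions, so the direction of the error matters. Stratifying randomisation by site does not deal with it, because courses are formed after randomisation and within one arm only.

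**Working it through.** **Inputs from the protocol article.** Courses of at most 12 (Intervention); 300 per arm, 30% v 40%, two-sided alpha 0.05, intended power 80% (Sample size considerations); pilot SD of AQoL change 0.21 (same section); clinically important AQoL change 0.05 (Outcome measures, item 1).

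**Assumptions.** ICC 0.01 to 0.05, since none is given. Average course size is not stated, so 12 (the maximum) and 8 are both shown. At 12 per course, 300/12 = 25 courses; at 8, 300/8 = 37.5, about 38.

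**Step 1: the plan's own figure.** The pooled two-proportion formula gives n per arm = [1.96√(2 × 0.35 × 0.65) + 0.8416√(0.30 × 0.70 + 0.40 × 0.60)]² / 0.10² = (1.322 + 0.565)² / 0.01 ≈ 356. Unpooled variance gives 354, the arcsine method 356 and a continuity correction 376. With 300 per arm, two-sided power is 72.9%. The stated 300 is matched only by a one-sided test with continuity correction, which contradicts the two-tailed test that the article states. So the 600 contains no hidden margin for clustering.

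**Step 2: one-arm clustering.** With m people per course, the intervention-arm variance is multiplied by DE = 1 + (m − 1) × ICC. The control arm is not inflated.

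- Ratio of true to reported standard error = √[(1 + DE)/2].
- Type I error of a nominal 5% test = 2[1 − Φ(1.96/ratio)].
- Power for 30% v 40% = Φ[(0.10 − 1.96 × SE0)/SE1], where SE0 = √[0.35 × 0.65 × (1 + DE)/300] and SE1 = √[(0.21 + DE × 0.24)/300].
- Power for the AQoL score = Φ[0.05/(0.21√((1 + DE)/300)) − 1.96]. This takes the pilot SD as the analysis SD and is shown because the named analysis uses the score rather than the proportion.

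Example, m = 12 and ICC 0.05: DE = 1 + 11 × 0.05 = 1.55; ratio = √1.275 = 1.129; type I error = 2[1 − Φ(1.736)] = 8.3%; SE0 = 0.0440, SE1 = 0.0440, power = Φ(0.314) = 62.3%.

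| Course size | ICC | DE | SE ratio | Type I error | Power, 30% v 40% | n per arm for 80% | Power, AQoL 0.05 |
|---|---|---|---|---|---|---|---|
| any | 0 | 1.00 | 1.000 | 5.0% | 72.9% | 356 | 83.0% |
| 12 | 0.01 | 1.11 | 1.027 | 5.6% | 70.6% | 376 | 81.0% |
| 12 | 0.02 | 1.22 | 1.054 | 6.3% | 68.4% | 396 | 79.0% |
| 12 | 0.05 | 1.55 | 1.129 | 8.3% | 62.3% | 456 | 73.3% |
| 8 | 0.01 | 1.07 | 1.017 | 5.4% | 71.4% | 369 | 81.8% |
| 8 | 0.02 | 1.14 | 1.034 | 5.8% | 70.0% | 382 | 80.5% |
| 8 | 0.05 | 1.35 | 1.084 | 7.1% | 65.9% | 420 | 76.7% |

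The type I column applies to an analysis that ignores course. The power columns apply to one that allows for it.

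**The case against.** **The ICC could be close to zero.** The format is prescriptive, leaders are trained and meet regularly, and the primary outcome is measured at 12 months, long after a 6-week course. This stands. A reader might infer that the standard errors are bound to be too small; the article does not support that, because it gives no ICC.

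**Individual randomisation protects the strict null.** If the programme changes nothing for anyone, course membership is irrelevant and the individual-level test is valid. Sorting by venue or time slot does not alter that. Type I inflation requires courses that truly differ around a zero mean effect. With SD 0.21, an ICC of 0.05 means a between-course SD of √0.05 × 0.21 ≈ 0.047 AQoL units, close to the 0.05 that the article calls clinically important. This also stands, and it makes the top of the range demanding. It does not rescue the intervals when the programme has some effect that varies by course.

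**Twelve is a maximum.** Smaller courses, non-attendance and loss to follow-up reduce the effect, which is why 8 per course is also shown.

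**Model detail belongs in an analysis plan.** An article need not give random-effect structures, and a separate plan could add a course term without contradicting this one. But the article names the 12-month model and fixes the sample size, both on independence, and no later model restores power to a fixed 600.

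**Leaders.** A reader might infer that every course has its own pair. The article says only that two leaders deliver the course, and the same people may run several.

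**Conclusion.** The point holds conditionally. The article describes a partially nested design and analyses and sizes it as if all participants were independent. If outcomes correlate within courses, the reported standard error is too small and power is below what the sample size section implies.

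For an ICC of 0.01 to 0.05 the effect is small to moderate, and at ICC 0.01 it is minor. The figures rest on the assumed ICC, equal course sizes, inflation of one arm only and a normal approximation. Applying a full design effect to both arms would overstate the problem.

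A reader might attribute the whole shortfall from 80% power to clustering. That would be wrong: the drop from 80% to 72.9% is a separate error in the base calculation, and clustering explains only the further loss of about 2 to 11 points at 12 per course (2 to 7 at 8). A change is recommended, but this is not a must-fix defect.

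**What to change.** - Record a course identifier for every intervention participant: the course to which the person was assigned, whether or not they attended, so that the comparison stays by randomised group. State in advance how anyone never assigned to a course is coded. Record leader identifiers too, because a course term alone does not capture leaders who run several courses.
- Fit the 12-month model with a random course effect in the intervention arm only, controls as singletons, and small-sample degrees of freedom (Kenward-Roger or Satterthwaite), since there may be only about 25 courses.
- Carry the same structure into the secondary outcomes and the cost and QALY comparisons, whichever method is used for those.
- Restate the power of 600 over a declared ICC range and realistic course sizes, after correcting the base calculation.

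The cost is one or two extra variables and some analysis wording. Intervals become slightly wider and the stated power lower. If the ICC proves close to zero, little is lost; if course membership is never recorded, the analysis may not be repairable afterwards.
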